## Abstract

Surgery is the primary treatment for tongue cancer. The goal is a complete resection of the tumor with an adequate margin of healthy tissue around the tumor.Inadequate margins lead to a high risk of local cancer recurrence and the need for adjuvant therapies. Ex vivo imaging of the resected surgical specimen has been suggested for margin assessment and improved surgical results. Therefore, we have developed a novel three-dimensional (3D) ultrasound imaging technique to improve the assessment of resection margins during surgery. In this research protocol, we describe a study comparing the accuracy of 3D ultrasound, magnetic resonance imaging (MRI), and clinical examination of the surgical specimen to assess the resection margins during cancer surgery. Tumor segmentation and margin measurement will be performed using 3D ultrasound and MRI of the ex vivo specimen. We will determine the accuracy of each method by comparing the margin measurements and the proportion of correctly classified margins (positive, close, and free) obtained by each technique with respect to the gold standard histopathology.

## 1. Introduction

Oral squamous cell carcinoma (SCC) is the eighth most common cancer worldwide, with less than 60% of the patients surviving more than 5 years [1]. In a study conducted at our center (Department of Otorhinolaryngology, Head and Neck Surgery, and Audiology, Rigshospitalet, University of Copenhagen, Copenhagen, Denmark), among 8299 oral cancer patients, it was found that the 5-year overall survival rate was 43% for women and 36% for men [2]. SCC of the tongue is the most common type of oral cavity cancer, and the primary treatment for patients with early stages of tongue SCC is surgery [3,4]. The main goal of surgical oncology is to entirely remove the tumor, along with a margin of healthy tissue surrounding it, to ensure proper cancer removal. At the same time, preserving as much healthy tissue as possible during tongue cancer surgery ensures the quality of life for the patient, maintaining vital functions such as swallowing and speaking after surgical treatment. Survival and the need for postoperative treatment are highly dependent on the accuracy of the surgical resection margins for the cancer. Inadequate surgical margins (margin ≤ 5 mm) may lead to a second resection [5]. The presence of positive (<1 mm) or close (1–5 mm) margins following cancer surgery leads to an increased risk of local cancer recurrence, reduces the chance of survival, and necessitates adjuvant treatments, such as radiotherapy or chemoradiation. In a study at our center investigating 1399 patients with oral squamous cell carcinoma (OSCC), 44% of the cases received adjuvant radiotherapy after surgery [6]. A recent retrospective analysis of 91 tongue SCC resections reported a total of 74% of the cases with close margins (1–5 mm) and 10% with positive margins (<1 mm) [7]. Given the significant impact of surgical precision on patient outcomes in oral squamous cell carcinoma (SCC), there is a pressing need for advanced intraoperative techniques to ensure complete tumor resection. The potential for positive surgical margins, which can lead to the necessity for additional treatments or even further surgery, underscores the critical need for more accurate and efficient intraoperative techniques. Therefore, the development and implementation of innovative approaches that can improve the rate of complete tumor resection are not only desirable but essential for enhancing surgical care and ultimately improving patient survival rates and quality of life [8].

Frozen section biopsy is routinely used for intraoperative margin evaluation in carcinomas of the head and neck. During this procedure, a separate tissue fragment representative of each margin is excised from the operation field after resection of the primary tumor and individually submitted as frozen sections to be microscopically evaluated by the pathologist. One of the main limitations of frozen section analysis is that only a few margins (the ones which are nearest to the tumor) can be examined during surgery [9]. Furthermore, this procedure increases the time in anesthesia by 30–60 min, increasing the risk of patient complications, as well as the treatment cost.

Another technique is the assessment of surgical margins by fluorescence imaging [10]. There are some challenges with this technique, such as the inter-/intra-variability of antibody agent concentrations between patients and within tumors [10]. However, the main challenge regarding the use of fluorescence imaging techniques is their limitation to the resection surface, as they do not provide information from the deep tissues inside the specimen. 

Perioperative or intraoperative MRI of surgical specimens has been suggested to improve the evaluation of the resection margins during cancer surgery. Heidkamp et al. implemented an intraoperative method to scan tongue cancer specimens but did not find it accurate in assessing resection margins [11]. In contrast, another study found MRI to reliably predict close or positive resection margins following tongue cancer surgery [12]. Still, MRI is a costly imaging modality, and other more portable imaging techniques may be preferable in the operating room.

Ultrasound is a portable, dynamic, cost-efficient imaging modality that can be used to provide high-resolution visualization of surgical specimens [13]. Often, 2D ultrasound has been used to visualize and measure in vivo tongue tumors [14,15,16]. A better prediction of tongue carcinoma staging is obtained using ultrasound compared to the use of manual palpation [14]. The depth of invasion (DOI) is an important factor for the T-classification of tongue SCC. Nilsson et al. assessed DOI in 40 patients with T1–T3 tongue SCC using 2D ultrasound, palpation, computed tomography (CT), and MRI, and it was concluded that 2D ultrasound was the most accurate method of evaluation [4]. A systematic review investigated the feasibility of 2D ultrasonography to measure the tumor thickness of oral cancer. It was concluded that there was a high correlation (r = 0.82, *p* < 0.001) between ultrasound and histopathology in tumor thickness measurement [15]. The result of another review article has shown the promising correlation between ultrasound and histopathology in tongue SCC for cervical lymph node metastases [16]. In another study, it has been argued that the tumor thickness measurements obtained by ultrasound can provide information about the cellular dissociation grading of tumor budding and cell nest size in early tongue cancer [17]. 

Moreover, 2D ultrasound has also been used for ex vivo imaging of tongue tumors [7,18,19]. De Koning et al. performed ex vivo 2D ultrasound examination of the margins in resected tongue SCC, which resulted in reduced need for local adjuvant treatment [7], and in another study, they showed that ultrasound-guided ex vivo tongue SCC resections improved the margin status and reduced the frequency of adjuvant radiotherapy by 50% [18]. Adriaanses et al. measured the tumor thickness using ultrasound and MRI and compared the results to those obtained by histology in 13 buccal mucosa SCC [19]. The accuracy of in vivo and ex vivo ultrasound for measuring tumor thickness was comparable to that of MRI. 

The limitations of most of the studies with 2D ultrasound imaging include the user-dependency and generation of dynamic two-dimensional image “slices” of the tissue using ultrasound. Instead, 3D ultrasound imaging is a promising approach to obtaining volumetric ultrasound images of the tumor and overcoming some of the problems of conventional B-mode ultrasound. The main advantages of 3D ultrasound compared to conventional 2D ultrasound imaging include the 3D visualization of the entire structure, less operator dependency, orientation-independent visualization, the measurement of quantitative attributes in three dimensions, the repeatability of the region of interest (ROI) examination, and the possibility of fusion with cross-sectional imaging modalities [20]. A list of research works, including some of the different 3D ultrasound imaging techniques and their applications, has been summarized in Table 1. 

There are studies reporting a higher diagnostic accuracy using 3D ultrasound compared to conventional 2D B-mode imaging [34,35]. We also conducted a pilot animal study to compare 3D ultrasound with CT, without a contrast agent, in measuring plane-by-plane tumor areas in an animal model. The result was a higher correlation between 3D ultrasound and the gold standard gross pathology [30]. In the head and neck region, freehand 3D ultrasound has previously been used for 3D imaging of jugular vessels [36,37], cervical lymph node assessment [38], and improving the tumor resection in glioma surgery [39].

Compared to MRI and CT, 3D ultrasound has the advantage that it can be performed immediately in the operating room in less than 10 min. It can also make an evaluation of the entire resected specimen, instead of the 0.1–1% samples sent for frozen section analysis [18,40].

Bekedam et al. used electromagnetically tracked ultrasound imaging to scan eight tongue cancer specimens immediately after excision [21]. The specimen and the tumor were segmented manually by a radiologist, and the margins were computed in 3D by calculating the closest Euclidean distances between the segmented specimen and the tumor boundary. The borders were more difficult to distinguish in some of the specimens due to small echogenicity differences between the tumor and healthy tissue. Even though the use of electromagnetic sensors is one of the most cost-effective methods for localization in freehand 3D ultrasound systems, their main drawback is their metal sensitivity [20]. Table 2 summarizes some of the publications focusing on surgical margin assessment.

In the current protocol, we introduce a novel approach to the assessment of resection margins in tongue SCC. We propose the application of 3D ex vivo ultrasound using a mechanical arm and a custom-made setup (3Sonics). This technique represents a significant advancement in the field, as it offers a portable, cost-effective, and efficient alternative to existing 3D ultrasound imaging methods. Unlike other imaging techniques, our proposed 3D ultrasound imaging technique does not rely on any type of sensor for probe position tracking, simplifying its operation and potentially increasing its accessibility and usability in various clinical settings. 

Furthermore, our method allows for a comprehensive comparison of the 3D ultrasound outcomes with results from MRI and clinical examination of the surgical specimen by a surgeon. This multi-modal approach enhances the robustness of our study and provides a more comprehensive understanding of the resection margins. The diagnostic accuracy of our method will be evaluated by computing the correlation of these three approaches to the final histopathology report, the gold standard in cancer.

## 2. Research Question

In patients surgically treated for oral tongue squamous cell carcinoma, what is the accuracy of 3D ultrasound compared to clinical examinations and MRI in the assessment of tumor resection margins?

## 3. Materials and Methods

The diagnostic accuracy study will be conducted at the Department of Otorhinolaryngology, Head and Neck Surgery, and Audiology, University Hospital of Copenhagen, Rigshospitalet (RH), Copenhagen, Denmark. The protocol adheres to recommendations for interventional trials described in the SPIRIT and STARD guidelines [47]. 

Patients diagnosed with tongue SCC will be invited to participate in the study. All participants meeting the inclusion criteria (described in Section 3.1) will undergo a preoperative in vivo ultrasound scan to measure the depth of invasion. Perioperative ex vivo 3D ultrasonography of the resected tongue tumor will then be performed. Furthermore, the surgeon will assess the surgical margins by clinical examination of the resected specimen ex vivo. Then, the surgical specimen will be MRI scanned at Department of Radiology immediately after surgery. Afterwards, the surgical specimen will be transferred to the pathology department for a formalin fixation procedure. On the day after the surgery, the surgical specimen will also be scanned by 3D ultrasound after formalin fixation. Surgical margin assessment results from the surgeon assessment, MRI, and the 3D ultrasound scan of the surgical specimen will be correlated to the final histopathology report. 

### 3.1. Eligibility Criteria

We will invite patients with tongue cancer scheduled to undergo surgical treatment at Rigshospitalet. The department performs all oncological surgical treatment of head and neck cancer for a population of about 2.6 million people from the Eastern Region of Denmark (comprising 46% of the Danish population), as well as Greenland and the Faroe Islands. Patients who meet the inclusion criteria (see Table 3) and agree to participate in the study will be enrolled in the trial.

### 3.2. Perioperative Assessment of Margins 

#### 3.2.1. Surgical Specimen Examination by the Surgeon

A standard examination of the surgical specimen will be performed in the operation theater by the surgeon in order to assess the margins after resection. This usually includes inspection and palpation of the surgical specimen to assess if there are close/positive margins. Additionally, the surgeon will evaluate the margins at five specific areas (anterior, posterior, medial, lateral, and profound) and estimate the closest distance in mm from the tumor to the resection (free margin) for each area. See Figure 1 for the schematic of the definition of the margin measurement directions.

Then, the surgeon will attach the resected specimen to a piece of cork using pins and will mark the directions.

#### 3.2.2. 3D Ultrasound Scan (3Sonics) of the Surgical Specimen on-Site

In the operation theater, the surgical specimen will undergo a 3D ultrasound scan. The 3D ultrasound scan will be performed using a portable custom-made setup, which we have named “3Sonics”. See Figure 2 for the different components of the 3D ultrasound imaging solution.

The 3D ultrasound imaging setup includes a slider (motorized mechanical arm) to move the transducer at a constant speed. A custom-made probe holder is connected to the slider to attach the ultrasound transducer and adjust the distance of the ultrasound probe front-face to the specimen in the depth direction. A water bath is designed to submerge the surgical specimen in saline water. We will pin a small plastic marker onto the cork next to the specimen for calibration and retrieval of the coordinate system. We have made a customized program in MATLAB (www.mathworks.com (accessed on 5 July 2023)) to generate 3D ultrasound volumes of the ex vivo surgical specimens. We will use an ArtUs EXT-1H ultrasound system (TELEMED, UAB Savanoriu, Lithuania) with a linear probe (L18-7H30-A5), which is ideal for near-field imaging and which provides detailed images of superficial structures. This probe has 192 elements, a 7–18 MHz frequency range, and a 30 mm field of view. The resolution in the probe sweep direction is 0.06 mm. Based on the inclusion criteria, including tumors with T1–T3 staging, we do not expect to scan depths greater than 4–5 cm, which will allow for high-resolution ultrasound scans. The ultrasound image optimization will be performed at the center position of the specimen prior to the mechanical sweep of the probe. The image optimization will mainly include the depth, frequency, gain, and focus adjustment to ensure the minimum required depth, the highest possible resolution and contrast, and the focus point at approximately the center of the tumor region. To minimize the artifacts, we will ensure that the ultrasound probe is correctly positioned and oriented. The total scanning time with setup adjustment and data acquisition has been estimated in pilot tests to be less than 10 min. The volume construction and calibration of the ultrasound data will be performed using the custom-made script in the commercially available programming tool MATLAB 2022b (www.mathworks.com (accessed on 5 July 2023)). 

Following the surgery, two experienced head and neck surgeons will manually segment the tumor region on the 3D ultrasound images. This process will involve identifying and delineating the tumor boundaries based on the echogenicity differences between the tumor and the surrounding healthy tissue. Segmentation will be conducted using the ITK-SNAP segmentation software (www.itksnap.org (accessed 5 on July 2023)) [48], a widely used and validated tool for medical image segmentation. The surgeons will measure the smallest margin (anterior, posterior, lateral, medial, and deep margin). The segmentation process will be performed on approximately 10–15 equally distanced planes throughout the tumor volume. These planes will be selected to provide a comprehensive representation of the tumor and its spatial relationship with the surrounding tissue. The segmented regions from these planes will then be interpolated (using the interpolation tool in ITK-SNAP) to construct a 3D representation of the entire tumor structure. This approach allows for a detailed visualization and measurement of the tumor and its margins from multiple perspectives.

In addition to the overall tumor segmentation, the surgeons will measure the deep margin at every segmented plane. This step will provide a detailed plane-by-plane assessment of the deep margin, which is crucial for determining the adequacy of the resection. The measurements from the 3D ultrasound will then be correlated with the histopathology results to evaluate the accuracy of the ultrasound-based measurements.

#### 3.2.3. MRI Scan of the Surgical Specimen in the Radiology Department

Immediately after the tumor resection, clinical examination by the surgeon, and the 3D ultrasound scan at the operation theater, the ex vivo surgical specimen will be transferred to the radiology department to allow for the acquisition of an MRI scan. The specimen will be oriented to maintain the same orientation as the 3D ultrasound scan. The surgical specimen pinned to the cork will be enclosed in a plastic box to ensure a stable positioning of the specimen and to minimize the possible pollution at the MRI setup.

A 1.5T MRI scan (Artist, GE Healthcare) will be performed using a wrist radiofrequency (RF) coil and a scan protocol with T2-weighted 2D MRI (1.0 mm slice thickness). The total examination time will be approximately 15 min. Two radiologists consultants will assess the surgical margins and the tumor region on the MRI scans over two rounds, similar to the procedure explained at Section 3.2.2.

#### 3.2.4. Tissue Preparation and Histopathology

After conducting the MRI scan in the radiology department, the surgical specimen will be returned to the pathology department for formalin fixation. 

In the pathology department, the samples will be treated using standard procedures to create formalin-fixed, paraffin-embedded (FFPE) blocks of tissue. The samples are first formalin-fixed with 10% formaldehyde for 24 h. Before starting the slicing procedure of the specimen by the pathologist, the formalin-fixated specimen will again undergo 3D ultrasound. Then a pathologist will perform parallel slicing, with almost equal intervals (~2 mm). The slices are then transferred to cassettes for further processing and embedded in paraffin to form FFPE blocks, which are cut at 4 μm and mounted on glass slides. Afterwards, the slides will be stained with hematoxylin and eosin (H&E) to visualize the tissue under the microscope. Two pathologists will assess the surgical margin status and will delineate the tumor on the slides. The tumor volume in milliliters (mL) will be estimated by the multiplication of the tumor area per slice and the cutting intervals. The pathologist will also measure the smallest margin at the posterior, anterior, lateral, medial, and profound directions (as described in Figure 1). The average measurement obtained by the two pathologists will be considered as the gold standard.

## 4. Clinical Outcome Definition

We will compare the surgical margin assessment in tongue cancer specimens by comparing three index tests (clinical examination, 3D ultrasound, and MRI) with the post-surgical histopathology assessments as the reference standard. 

The primary outcome will be reported as:The perioperative measurement of resection margins (mm) at five directions (Figure 1) with clinical exam and imaging compared to the post-surgical histopathology results (reference standard).The image-by-image comparison of the depth of invasion measurement (mm) from 3D ultrasound/MR imaging and histopathology slides.The depth of invasion (mm) comparison between in vivo and ex vivo ultrasound.The number of margins correctly classified as free (>5 mm), close (1–5 mm), or positive (<1 mm) margins by 3D ultrasound and MRI using histopathology findings as the reference.

The secondary outcome will be: The number of cases requiring adjuvant treatments (surgery or chemo/radiotherapy) due to T-site residuals.A change in tumor volume and resection margin measurements with 3D ultrasound imaging before and after formalin fixation.The time usage (minutes) and cost estimation for perioperative 3D ultrasound and MRI.

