The intra- and interobserver variability will be quantified by calculating the intraclass correlation coefficient (ICC). The ICC measures the reliability of the measurements between the two observers and is the measure of the degree of agreement among the observers in their assessment of margin status.

We will also classify the data into three categories of positive (<1 mm), close (between 1–5 mm), and free (>5 mm) margins. For each included case, we will compare the accuracy of each index test by computing the proportion of correctly classified margins with respect to the reference standard class. We will use the McNemar test to determine if the proportions of categories in the index tests differ significantly from those of the reference standard (paired categorical data). The results will be considered statistically significant when *p* < 0.05, with a 95% confidence interval. 

The mean time spent on delineation by the operators will be recorded and reported in minutes. Data will be analyzed with commercially available software (RStudio Team-2023). RStudio: Integrated Development for R. RStudio, Inc., Boston, MA, USA.

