## 6. Power Calculation and Inclusion Period

A power calculation was based on the expected change in frequency between the free margin status when diagnosed by ultrasound imaging of the surgical specimen and when evaluated using the conventional procedure in the operation theater, without using ultrasound. The sample size needed to compare two independent binomial proportions is calculated to achieve a significance level of 0.05 and 90% power. The power calculation is based on results from Koning et al. [18] that found the frequency of free margin status to be 55% using ultrasound and 16% in the conventional cohort. A 2-sample paired binary sample size calculation results in the sample size of n = 27. By estimating a 10% drop-out rate, due to technical reasons, we will aim to include 30 cases. 

In Denmark, oral cavity cancer is the second most common head and neck cancer, and it has previously been reported with an incidence of 3.5 pr. 100,000. The uptake for the Rigshospitalet Center averages more than 90 cases annually, with 1/3 being tongue tumor cases [2,49]. In Denmark, all cancer investigations and treatments take place in public hospitals, free of charge, and financed by taxes. Based on the Copenhagen oral cavity squamous cell carcinoma database [6], we expect more than 30 patients annually to be diagnosed with tongue SCC, and these are the potentially eligible participants. Some of these patients will not fulfill the inclusion criteria, and some will decline to participate in the study. Therefore, we expect to include roughly 60% of the patients over a 1.5 year period. All enrolled patients are included in the analysis, with an intention-to-treat assumption [50]. We will register the age, sex, and final pathology staging of all the eligible participants to assess the comparability of the indexed population to the recurrent general tongue cancer population.

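### Section 4 names four different quantities as the primary outcome with no order of precedence, and the sample size rests on a contrast that is none of them

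*Protocol article*

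**What the plan says.** Section 4 (Clinical Outcome Definition) opens its list in the singular, "The primary outcome will be reported as", and gives four items:

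1. "The perioperative measurement of resection margins (mm) at five directions (Figure 1) with clinical exam and imaging compared to the post-surgical histopathology results"
2. "The image-by-image comparison of the depth of invasion measurement (mm) from 3D ultrasound/MR imaging and histopathology slides"
3. "The depth of invasion (mm) comparison between in vivo and ex vivo ultrasound"
4. "The number of margins correctly classified as free (>5 mm), close (1–5 mm), or positive (<1 mm) margins by 3D ultrasound and MRI"

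No order, co-primary rule or success criterion is attached. The same section says that "three index tests (clinical examination, 3D ultrasound, and MRI") are to be compared with histopathology, yet item 4 names only two of the three.

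Section 5 (Statistics) assigns a paired t-test to the mm differences. It sets p < 0.05 for the Pearson correlations and for the plane-by-plane deep margins. After the McNemar test it adds a general sentence, "The results will be considered statistically significant when" p is below 0.05. It also plans Bland–Altman plots with 95% confidence intervals.

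Section 6 says the sample size was "calculated to achieve a significance level of 0.05 and 90% power". The contrast there is the frequency of free margins, 55% with ultrasound and 16% in a conventional cohort.

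**The concern.** A primary outcome exists so that one result, chosen in advance, answers the research question. Section 2 asks how accurate 3D ultrasound is for resection margins compared with clinical examination and MRI. With four unranked primaries, the first spread over five directions and three index tests, the results could point different ways. Ultrasound might classify margins well but show bias in the deep direction, or correlate strongly while misclassifying close margins. Nothing in the article says which result would then be the study's answer, so a favourable measure or direction could be put forward as the primary finding. The stated level and power do not help, because they describe a different contrast.

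**Working it through.** **Step 1. Does another section settle which outcome leads?** It does not.

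| Place | How accuracy is to be judged |
|---|---|
| Abstract | Margin measurements and proportion correctly classified |
| Section 1, last paragraph | Correlation with histopathology |
| Section 4 | Four quantities, unranked |
| Section 6 | Free-margin frequency with and without ultrasound |
| Section 8 | A higher diagnostic rate than MRI and clinical examination |

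Item 3 compares two ultrasound measurements of depth of invasion. It involves neither resection margins nor histopathology, so it cannot answer Section 2.

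**Step 2. Reproduce the sample size and see what it covers.** Inputs from Section 6: 0.55, 0.16, level 0.05 (taken as two-sided, which the text does not state), power 90%, drop-out 10%.

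- Unpooled formula: n = (z₀.₉₇₅ + z₀.₉₀)² × [p₁(1−p₁) + p₂(1−p₂)] / (p₁−p₂)²
- (1.960 + 1.282)² ≈ 10.51; 0.2475 + 0.1344 = 0.3819; 0.39² = 0.1521
- n = 10.51 × 0.3819 / 0.1521 ≈ 26.4, so 27; 27 / 0.9 = 30

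This matches the stated 27 and 30. For independent groups, 27 is the number per group. The figure concerns how often margins are free, not how often a test classifies them correctly, so it gives no power for any item in Section 4.

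**Step 3. What Section 5 does with each item.**

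| Item | Analysis named | Threshold |
|---|---|---|
| 1. Margins in mm | Paired t-test, Pearson, Bland–Altman | p < 0.05 for Pearson; t-test only under the general sentence |
| 2. Image-by-image depth of invasion | None by name (the plane-by-plane test concerns the deep margin) | None specific |
| 3. In vivo against ex vivo depth | Correlation, reported | None |
| 4. Margin class | Proportion correct, McNemar | p < 0.05 |

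**Step 4. Size of the error rate for item 1.** The article does not say whether directions are tested separately or pooled, so both cases are shown. All null hypotheses are taken as true and each test is two-sided at 0.05.

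- Separate: 3 index tests × 5 directions = 15 t-tests. If independent, 1 − 0.95¹⁵ = 0.537.
- Separate and correlated: the correlation between tests is not given. Simulating 200,000 sets of 15 equally correlated z-tests gives 0.46 at correlation 0.3, 0.36 at 0.5 and 0.20 at 0.8.
- Pooled, one test per index test: if independent, 1 − 0.95³ = 0.143.

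**Step 5. Clinical examination.** Section 2 requires it as a comparator, the opening of Section 4 counts it as an index test, and Section 5 computes the proportion correct for each index test. Only item 4 of Section 4 leaves it out.

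**The case against.** The best defence is that this is a small diagnostic accuracy study with largely descriptive aims. The 0.05 values are per-test thresholds, Bland–Altman analysis with intervals is already planned, and a multiplicity rule may sit in an analysis plan that is not shown. Much of this stands, and it rules out several stronger readings.

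- A reader might infer that all four primaries are tested at p < 0.05. Section 5 does not say so: item 3 is only reported, and no test of depth of invasion is named for item 2.
- A reader might infer that the plan breaks its own 0.05 level. It claims no familywise level, so none is broken; it sets none.
- A reader might take 54% as the plan's error rate. That figure needs 15 separate, independent tests, which the text does not specify.
- A reader might take the error rate as the chance of a falsely favourable result. The t-tests and McNemar tests set each index test against histopathology, so a false positive is a spurious finding of bias or of differing proportions. It does not show spurious accuracy.
- A reader might infer that clinical examination is left out of the classification analysis. Section 5 includes it, so the fault is in the wording of Section 4.

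The defence does not reach the main point. An analysis plan can hold details of multiplicity, but choosing the primary outcome belongs to the protocol, and this one chooses four without ranking them.

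**Conclusion.** The point holds in this form: four different quantities share the primary label with no precedence or success rule, and the only contrast with a stated level and power is none of them. This can be read directly from Sections 4 to 6 and rests on no assumption. The main harm is the lack of one pre-specified answer and the room to pick a measure or direction after the data are seen.

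Error inflation is the lesser part, and its size depends on assumptions. For the mm margins alone it is about 14% with three pooled independent tests, 20–46% with 15 separate tests at assumed correlations of 0.8–0.3, and 54% with 15 independent tests. All are above 5%, but they describe spurious findings of bias. The missing clinical examination in item 4 is a real inconsistency that the analysis in Section 5 already points the way to resolving.

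**What to change.** - **Section 4:** name one primary comparison that answers Section 2. One example is the proportion of margins correctly classified against histopathology by 3D ultrasound compared with clinical examination, with the same comparison against MRI as a key secondary. Add clinical examination to the classification outcome.
- **Sections 4 and 5:** make the mm margins and both depth-of-invasion outcomes secondary, reported as estimates with 95% confidence intervals and without claims of significance. The planned Bland–Altman analysis already serves the mm margins. If the margin is the unit of the primary, the interval should allow for five margins coming from one patient.
- **Section 6:** say that 27 (30 with drop-out) was sized on free-margin frequency, and give the precision or power that 27 cases provide for the named primary.

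The change needs no new data and no new procedures. Its cost is rewording plus one new calculation. Three outcomes lose the primary label, and the 90% power statement cannot be kept for the new primary unless that calculation supports it.
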